## Methods/design

### Study design

This is a multicenter, randomized, single-blind, placebo-controlled clinical trial, with superiority in the framework. After a run-in period within 7 days, 270 eligible participants will be randomized to the test group (TCM granules with chemotherapy) or the control group (placebo with chemotherapy) in a 1:1 ratio. All participants will undergo a treatment period of 12–18 weeks and a follow-up period until death. During the treatment period, both groups have to receive chemotherapy for 4–6 cycles. In the interphase of chemotherapy (days 6–21 of each cycle), participants in the test group will take TCM granules while those in the control group will take placebo granules for 15 days. Visits will be performed at days 0, 21, 42, 63, 84, 105, and 126 in the treatment period, and the last week of every 3 months (approximately 90 days) during the subsequent follow-up period. The study is scheduled to open from December 2018 to December 2021. The recruiting was started in June 2019 and lasted for 24 months. The endpoint of follow-up is the date of death or December 31, 2021 (Fig. 1).

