#### Chemotherapy

All the eligible participants will undergo 4–6 cycles (21days per cycle) chemotherapy with the standard regimens recommended by the National Comprehensive Cancer Network (NCCN) clinical practice guidelines in SCLC (Version 2, 2018), and the preferred one is EP (Etoposide 100 mg/m^2^ on days 1–3, Cisplatin 75 mg/m^2^ on day 1, every 21 days).

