### Assessments and time-points

Assessments will be performed at baseline and every protocol-defined interval (Table 2) until the occurrence of death or study completion.

**Table 2 Tab2:** Schedule of data collection

	Screening and baseline	Treatment period						Follow-up period			
**Visits**	**--**	**1**	**2**	**3**	**4**	**5**	**6**	**7**	**8**	**9**	**……**
**Time points (days)**^**a**^	**− 7 to 0**	**21**	**42**	**63**	**84**	**105**	**126**	**195**	**285**	**375**	**……**
**Time windows (days)**	**--**	**±7**	**±7**	**±7**	**±7**	**±7**	**±7**	**±21**	**±21**	**±21**	**±21**
Informed consent	×										
Inclusion and exclusion criteria	×										
Survival state		×	×	×	×	×	×	×	×	×	×
General data	×										
History of diagnosis and treatment	×										
ECOG-PS	×										
Imaging examination	×		×		×		×	×	×	×	×
ORR			×		×		×	×	×	×	×
FACT-L scale	×	×	×	×	×	×	×	×	×	×	×
TCM symptoms scale	×	×	×	×	×	×	×	×	×	×	×
Tumor markers	×	×	×	×	×	×	×				
Blood, urine, stool routine examination	×	×	×	×	×	×	×				
Liver and renal function examination	×	×	×	×	×	×	×				
Electrocardiogram	×	×	×	×	×	×	×				
AEs		×	×	×	×	×	×	×	×	×	×
Compliance assessment		×	×	×	×	×	×	×	×	×	×
Drug combination		×	×	×	×	×	×	×	×	×	×

*Abbreviations: ECOG-PS* Eastern Cooperative Oncology Group performance status, *ORR* objective response rate, *FACT-L* Functional Assessment of Cancer Therapy-lung carcinoma, *TCM* traditional Chinese medicine, *AEs* adverse events

^**a**^At the end of each cycle in the treatment period and every 3 months in the follow-up period

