#### Secondary outcomes

The secondary outcomes are as follow:

PFS: From randomization to occurrence of imaging-based disease progress (PD), which is assessed by the investigators.

ORR: Imaging examinations for the target lesions will be done at days 0, 42, 84, and 126 during the treatment period and every 90 days during the follow-up period. The tumor response is evaluated according to standards of Response Evaluation Criteria in Solid Tumors (RECIST) Version 1.1, rating as complete response (CR), partial response (PR), stable disease (SD), or PD. ORR is the ratio of participants rated as CR and PR to total cases.

QoL: Functional Assessment of Cancer Therapy-lung carcinoma (FACT-L) scale and TCM syndromes scale are used for the evaluation of QoL. The participants will answer the questionnaires in FACT-L independently with the assistance of investigators, covering physical, social and family, emotional, and functional statuses, as well as lung cancer module. The total score of FACT-L is calculated by adding up the scores of each item. TCM syndrome scale is designed to record the extent of several typical symptoms such as cough, phlegm, fatigue, shortness of breath, and loss of appetite. 0, 1, 2, and 3 points represent “none”, “mild”, “moderate”, and “severe”, respectively. QoL data are collected at baseline and in each visit.

Tumor markers: the commonest tumor markers, NSE and proGRP, are tested at days 0, 21, 42, 63, 84, 105, and 126 during the treatment period.

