The study still has some limitations as follows. First, the study was not designed as a double-blind trial. The traditional double-blind double-mimic method is not affordable and suitable for this study of multiple TCM prescriptions. Therefore, we finally chose single-blind which conforms to the complexity and feasibility of TCM and implemented it strictly to control the risk of reveals. Second, the assessment of OS may be influenced by confounders. Since the study intents to evaluate the long-term efficacy of TCM granules with chemotherapy, the TCM intervention period is designed as 4–6 cycles, synchronizing with chemotherapy. While in recent years, the second-line or later regimens are continuously refreshed by ICIs [19], anlotinib [20], lurbinectedin [21], and rovalpituzumab tesirine (Rova-T) [22]. As the study gives priority to the patient’s interests, the investigators should respect participants’ choices of positive treatment after PD. Thus, the second- and third-line regimen may become vital factors for prognosis. As a remedy, we require the investigators to keep detailed records of regimen participants using after PD and provide them to statisticians to build a more realistic and reasonable regression model.

In conclusion, the study’s result will provide a high-level evidence for TCM granules using with chemotherapy on the first-line treatment of ES-SCLC.

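### Tumor markers are listed to day 126 for everyone, but the schedule implies none after the last cycle, so late marker comparisons would be selected by cycle number

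*Protocol article*

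**What the plan says.** Study design (Protocol article) fixes the length of treatment: "All participants will undergo a treatment period of 12–18 weeks and a follow-up period until death", and "both groups have to receive chemotherapy for 4–6 cycles". The Chemotherapy section gives the cycle length: "All the eligible participants will undergo 4–6 cycles (21days per cycle) chemotherapy". The Discussion adds that "the TCM intervention period is designed as 4–6 cycles, synchronizing with chemotherapy", so granules or placebo stop when the cycles stop.

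Three places put days 105 and 126 inside the treatment period, with no exception for participants given four or five cycles:

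- Study design: "Visits will be performed at days 0, 21, 42, 63, 84, 105, and 126 in the treatment period".
- Secondary outcomes: "NSE and proGRP, are tested at days 0, 21, 42, 63, 84, 105, and 126 during the treatment period".
- Table 2, where the row "Tumor markers" has seven crosses (baseline and visits 1 to 6) and none under follow-up.

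Footnote a to Table 2 defines the time points differently: "At the end of each cycle in the treatment period and every 3 months in the follow-up period".

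Statistical analysis plans a t-test or repeated-measures ANOVA for quality of life and tumor markers, or analysis of covariance if baseline scores are not similar. It names no marker time point.

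**The concern.** The day list fits only a participant who receives six cycles. For anyone given fewer, the last one or two listed days fall after treatment has ended, and the document gives two rules for them. The fixed day columns sample everyone to day 126. The footnote samples at cycle ends only and then moves the participant into follow-up, where no marker is taken.

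Under the footnote, values at days 105 and 126 exist only for participants who continued past four or five cycles. That status arises after randomisation, and the article states no rule for it. If it differs between arms and is related to the marker, a late between-arm comparison can show a difference without any marker effect. Even if it is the same in both arms, an analysis that needs all seven visits discards every participant given fewer than six cycles.

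**Working it through.** **Reproducing the stated treatment period.** Cycles × 21 days:

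| Cycles | End of treatment | Weeks | Listed marker days after the end |
|---|---|---|---|
| 4 | day 84 | 12 | 105 (+21 days), 126 (+42 days) |
| 5 | day 105 | 15 | 126 (+21 days) |
| 6 | day 126 | 18 | none |

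This matches the stated 12 to 18 weeks exactly.

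**Which rule does Table 2 support?** The first follow-up visit is at day 195 with a window of ±21, that is days 174 to 216. Taking the three-month interval as 90 days, as Study design does, end of treatment + 90 gives 84 + 90 = 174, 105 + 90 = 195 and 126 + 90 = 216. The window covers exactly these three cases. The schedule therefore appears to move a four-cycle participant into follow-up at day 84. Since Table 2 has no follow-up markers, the last marker falls at day 84, 105 or 126 for four, five or six cycles.

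**Selection at day 105 (illustration; all inputs assumed).** Assume no marker effect, 70% of one arm and 50% of the other continuing past four cycles, and a correlation ρ of 0.3 to 0.5 between the log marker and stopping at four. Assume also 135 per arm with no other loss. With a threshold model, the mean standardised marker among those continuing is −ρ·φ(c)/p, where p is the proportion continuing and c the corresponding normal cut-point.

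- p = 0.5: −0.798ρ. p = 0.7: −0.497ρ. Difference: 0.301ρ.
- ρ = 0.3: 0.090 SD. ρ = 0.5: 0.151 SD.
- Numbers at day 105: 135 × 0.7 = 94.5 and 135 × 0.5 = 67.5. SE = √(1/94.5 + 1/67.5) = 0.159.
- Rejection = P(|Z + bias/SE| > 1.96): 8.8% for ρ = 0.3 and 15.7% for ρ = 0.5, against a nominal 5%.

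If continuation is equal in both arms, this model gives no bias.

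**Loss of information with equal continuation (also assumed).** Suppose 40% stop at four cycles and a further 10% at five, in both arms. On-treatment numbers per arm are 135 × 0.6 = 81 at day 105 and 135 × 0.5 = 67.5 at day 126. Power for an assumed difference of 0.35 SD falls from 82% with 135 per arm to 53% at day 126. With 20%, 60% or 80% stopping at four cycles (and again 10% at five), power at day 126 is 67%, 35% or 15%. A complete-case analysis over all seven visits keeps only the six-cycle participants, here half of those randomised.

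**The case against.** The strongest reply is that the document largely answers the question itself. The footnote, the restriction of marker days to the treatment period and the day 195 window all point the same way, so the day list reads naturally as the maximum schedule for six cycles. The choice of visits and the handling of absent values may sit in an analysis plan that is not shown. No test at day 105 or 126 is specified, and the article does not say that the repeated-measures analysis is complete-case.

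Much of this stands, and it rules out several stronger readings:

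- A reader might infer that the late samples mix on-treatment and off-treatment values. That follows only if sites sample by the fixed day columns, which is the less supported reading, and such mixing is not in itself a bias between arms.
- A reader might take the 9% to 16% as a false-positive rate at day 126. The calculation uses everyone who continues past four cycles, which is the day-105 population. It would apply to day 126 only if nobody stopped at five.
- A reader might take it as given that cycle number depends on response or tolerance. That is plausible, but the article states no rule, so both the direction and the size of any bias are assumptions.
- A reader might treat day 84 as free of selection. It is not, because death and withdrawal also occur before then.

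The reply does not remove the point. The natural reading is the one under which late values come from a selected group. The listed visits and the named methods lead to that comparison unless a common window is set. An analysis plan also cannot recover samples that sites did not take, and three places in the article still list those days without limit.

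**Conclusion.** The point holds as a minor one. The article's own figures end treatment at day 84, 105 or 126, while its marker schedule runs to day 126 without exception. On the better-supported reading, markers after day 84 are absent by design for four-cycle participants, and day 126 is also absent for five-cycle participants. A late t-test or a complete-case repeated-measures ANOVA over the listed visits would then be selected by cycle number.

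Bias needs two conditions: continuation that differs between arms, and continuation that is related to the marker. Its size cannot be computed from the documents, and the 0.09 to 0.15 SD at day 105 rests entirely on assumed inputs. Loss of participants at the late visits needs neither condition, only that some receive fewer than six cycles. The documents do not support a claim that the trial's conclusions are at risk: the marker schedule concerns one secondary outcome and does not affect overall survival.

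**What to change.** Make days 0 to 84 the stated window for the marker comparison. Use change from day 0 to day 84, with repeated measures over days 21 to 84 in a mixed model that keeps participants with incomplete visits. Report days 105 and 126 descriptively. Reconcile Study design, Table 2 with its footnote, and Secondary outcomes so that they say the same thing about who is sampled on those two days. Safety assessment uses the same day list and can be aligned in the same edit.

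The cost is a sentence of analysis wording and a clarifying line in the schedule; no treatment changes. The downside is small: the formal comparison covers four cycles rather than six, and day 84 remains subject to loss from death and withdrawal.

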#### Safety assessment

The participants’ blood, urine and stool routine, liver and kidney function, and electrocardiogram were monitored at days 0, 21, 42, 63, 84, 105, and 126 during the treatment period. The AEs are categorized according to the National Cancer Institute's Common Terminology Criteria for Adverse Events (NCI-CTCAE) Version 4.03 and recorded overall the study.

### Register, ethical issues, and oversight

Before recruitment, we have registered the protocol in the Chinese Clinical Trial Registry (No. ChiCTR1900022991, 6 May 2019).

The study was ethically approved (2019L02-009-01) by the Research Ethical Committees at Beijing Hospital of the Traditional Chinese Medicine, Capital Medical University, and the other five participating sites. Now it is being conducted according to the principles of risks and benefits, privacy and confidentiality, informed consent, placebo using, etc., in the Declaration of Helsinki.

The oversight is in charge of Qihuang Contract Research Organization (CRO), through quarterly independently monitoring by clinical research associates (CRA) in terms of safety, quality, and progress of the study.

### Data management

PUCRI is responsible for data management. The data managers (DM) in PUCRI have built an EDC on the basis of CRF in REDCap system (Version 8.4.3) according to “data management and verification plan” drafted before. CRCs can type-in data to the EDC through their personal accounts. The errors or questions discovered by the system will be sent to the CRCs for answers. After all the data inputted without remaining questions, PI, sub-Is, and CRCs will lock the database within 4 weeks. Finally, the database will be exported by PUCRI and hand over to the statisticians. Only DMs have access to the final trial dataset.

### Statistical analysis

All data will be processed by a two-sided statistical test in SAS software 9.2 (the installation site’s authorization number: 11202165). *P*≤0.05 is defined as a statistical significance. Full analysis set (FAS), per-protocol set (PPS), and safety set (SS) will be created after data collection.

The statistical design is as follows:

For characteristics at baseline, continuous variables will be described with the use of mean (standard deviation) or median (quartile) based on the distribution. A T-test will be adopted if the normality and homogeneity of variance are satisfied; otherwise, the nonparametric test will be carried out. Categorical variables will be analyzed by the chi-square test or nonparametric test.

For OS and PFS, the Kaplan-Meier curve and the Log-rank test will be used to analyze the distribution of the survival function. And the factors selected in the univariate analysis will be brought into the Cox regression for further multivariate analysis.

For tumor response, the logistic regression or Ridit analysis will be used to compare the differences in ORR, while the proportion of CR, PR, SD, and PD will be compared by the CHM test because of the central effect.

For QoL and tumor markers, the T-test or RMANOVA will be used to compare the differences intra- or inter-groups if the two groups’ scores at baseline are similar. Or the covariance analysis will be used to correct for confounders if not.

For safety assessment, the AEs and their incidences should be recorded in detail.

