The primary objective of this RCT is to determine whether the TCM granules with chemotherapy can improve the OS in treating with ES-SCLC when compared with chemotherapy alone. The trial will also provide clinical evidence on the efficacy of TCM granules in progression-free survival (PFS), objective response rate (ORR), quality of life (QoL), and tumor markers of ES-SCLC, alongside a safety analysis.

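### For QoL and tumour markers the plan allows within-group or between-group tests at P≤0.05 without making the between-group contrast the efficacy test

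*Protocol article*

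**What the plan says.** The objectives at the end of the Background present these outcomes as evidence on the granules: "The trial will also provide clinical evidence on the efficacy of TCM granules in progression-free survival (PFS), objective response rate (ORR), quality of life (QoL"; tumour markers complete the same list. Under Study design the framework is superiority, with participants "randomized to the test group (TCM granules with chemotherapy) or the control group (placebo with chemotherapy) in a 1:1 ratio", and both arms are to receive 4 to 6 cycles of chemotherapy.

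The Statistical analysis section then gives the rule for QoL and tumour markers: "the T-test or RMANOVA will be used to compare the differences intra- or inter-groups if the two groups’ scores at baseline are similar". The alternative follows: "Or the covariance analysis will be used to correct for confounders if not". The same section opens with general rules for every outcome: "All data will be processed by a two-sided statistical test", and P "≤0.05 is defined as a statistical significance".

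Four measures fall under this rule: FACT-L, the TCM syndrome scale, NSE and proGRP. All four are taken at baseline and at the six treatment-period visits, and the two scales also during follow-up (Secondary outcomes; Table 2).

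**The concern.** The question set by the objectives and the placebo arm is whether the change differs between arms. A within-group t-test, or the time effect of a repeated-measures ANOVA, asks whether scores changed at all within an arm. The plan joins the two comparisons with a plain alternative, applies one significance threshold to all data, and does not say which comparison answers the efficacy question.

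Both arms receive first-line chemotherapy, and the TCM regimens section itself expects symptoms to shift in the course of treatment. The within-group null may therefore be false in both arms even if the granules do nothing. A within-group P value offered as support for the granules would give up the protection of the randomised placebo comparison. Noting that the change is significant in the TCM arm but not in the placebo arm does not restore it, because that pattern is not a test of the difference between arms. None of this depends on baseline imbalance or on non-normal data.

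**Working it through.** **The plan's own figure.** There is none to reproduce: the article states no error rate, power, mean change or SD for QoL or tumour markers.

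**Inputs**
- n = 135 per arm: the enrolment target in Sample size calculation.
- n = 80 per arm: an assumed lower number, to show the effect of deaths and dropout.
- Two-sided alpha = 0.05: Statistical analysis.
- d = mean change from baseline ÷ SD of the change score, the same in both arms, so the granule effect is zero. The value of d is an assumption, shown as a range.
- Normal change scores.

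**Step 1: within-group test.** The paired t statistic follows a noncentral t distribution with n − 1 degrees of freedom and noncentrality d√n. The rejection rate is p = P(|T| > t₀.₉₇₅,ₙ₋₁).
- n = 135: √135 = 11.62, critical value 1.978.
- n = 80: √80 = 8.94, critical value 1.990.

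**Step 2: TCM arm only.** The arms are independent with the same d, so the chance that the TCM arm is significant and the placebo arm is not is p(1 − p). Its maximum is 0.25, at p = 0.5.

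| d | d√n, n = 135 | p, n = 135 | p(1 − p), n = 135 | p, n = 80 | p(1 − p), n = 80 |
|---|---|---|---|---|---|
| 0 | 0 | 5.0% | 4.8% | 5.0% | 4.8% |
| 0.05 | 0.58 | 8.9% | 8.1% | 7.3% | 6.7% |
| 0.1 | 1.16 | 21.1% | 16.6% | 14.3% | 12.3% |
| 0.2 | 2.32 | 63.6% | 23.2% | 42.4% | 24.4% |
| 0.3 | 3.49 | 93.3% | 6.2% | 75.5% | 18.5% |
| 0.5 | 5.81 | 99.99% | 0.01% | 99.3% | 0.7% |

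At n = 135 the TCM-arm-only pattern peaks at about 25% near d = 0.17. It exceeds 10% only for d of about 0.06 to 0.27.

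**Step 3: between-group test.** The two means are equal under inert granules, so the two-sample t-test on change rejects at its nominal 5% whatever d is. In 20,000 simulated trials per setting at 135 per arm it rejected in 5.3%, 4.9%, 4.9% and 5.1% at d = 0.1, 0.2, 0.3 and 0.5.

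**The case against.** The strongest reply is that the plan never says a within-group P value will support a claim about the granules. Reporting change within each arm beside the comparison between arms is common, and the paired test is valid for its own null. The rejection rates above are its power against a null that is truly false; they become errors about the granules only if someone misreads them. The sentence also leans towards the between-group comparison: similar baselines in the two groups, and a covariance fallback if they differ, matter only when arms are compared. Repeated-measures ANOVA over two arms supplies the group and group-by-time terms. The article is a condensed account, and a fuller plan may rank the comparisons.

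Most of this stands, and it limits the point. A reader might infer that the sponsor intends to claim efficacy from within-arm tests; the text permits that but does not say it. A reader might also infer that chemotherapy is bound to push rejection far above 5%. The documents give no size for the change, and at d = 0.05 the rate at 135 per arm is only 9%. Nor does the TCM-arm-only pattern mislead often at every size of change: at 0.3 SD and 135 per arm it occurs in 6% of trials. Two-sided rejections also include deterioration, which could hardly be presented as benefit. Multiplying the problem by six visits would assume separate t-tests at each visit, whereas repeated-measures ANOVA takes the visits together.

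What the reply does not remove is the wording itself. The rule names the within-group test as an alternative, under the general P≤0.05 threshold, for outcomes declared to be efficacy evidence. An analyst could follow it to the letter and test the wrong null. That is a stated rule fixed badly, not a detail left for later.

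**Conclusion.** The point holds as a defect of wording with a real but conditional consequence. The plan does not make the between-group contrast the efficacy test for QoL and tumour markers, and the within-group test it also admits cannot answer the granule question.

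If that test were read as efficacy with inert granules, common changes of 0.1 to 0.3 SD would give false support in 21% to 93% of trials at 135 per arm and 14% to 76% at 80 per arm, against 5% for the between-group test. With no common change the rate is 5%. These sizes rest on an assumed common change, normal change scores and that misreading. The documents do not show that the misreading is planned.

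Only secondary outcomes are affected, and the log-rank comparison of overall survival is untouched. The change should be made, but it does not threaten the primary result.

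**What to change.** In Statistical analysis, replace the wording that offers within-group or between-group comparisons with, for example: The treatment effect on FACT-L, the TCM syndrome scale, NSE and proGRP is the between-group contrast (in repeated-measures ANOVA, the group or group-by-visit contrast), reported with its 95% CI and P value. Within-group changes are shown descriptively, as mean change with CI and without P values, and are not used to conclude on the granules.

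This can go into the protocol or the SAP before database lock. It needs no new data and no change of design. The downside is fewer nominally significant results to report.

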### Sample size calculation

The sample size was calculated by PASS 15.0 software. The model was established according to the log-rank test of survival analysis (bilateral side), with α=0.05 and power 1 – β = 0.8. Based on recent researches [15, 16], the median survival in ES-SCLC with first-line chemotherapy was approximately 8 months, which we estimated to be 4 months longer after TCM combined with chemotherapy. The recruitment period was set as 24 months while the total time was 36 months. The minimum sample size was calculated as 112 in each group. Considering a 10% loss, we sought to enroll at least 270 (135 per group) participants in the study.

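### Baseline adjustment of quality of life and tumour markers depends on whether the arms look similar at baseline, so the method is chosen after seeing data and precision is lost by default

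*Protocol article*

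**What the plan says.** The Statistical analysis section states a two-branch rule for QoL and tumour markers. The first branch reads: "the T-test or RMANOVA will be used to compare the differences intra- or inter-groups if the two groups’ scores at baseline are similar". The second reads: "the covariance analysis will be used to correct for confounders if not". The section does not say what counts as similar, what decides between the t-test and the repeated-measures ANOVA, or which covariates the second branch would include. Testing is two-sided, with significance at P≤0.05.

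The baseline values needed for adjustment are already collected. Under Secondary outcomes, "QoL data are collected at baseline and in each visit", and the markers NSE and proGRP are measured every 21 days from day 0 to day 126. Table 2 continues the FACT-L questionnaire into follow-up, at days 195, 285, 375 and beyond.

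**The concern.** Allocation is central and 1:1, so a baseline difference between the arms can only be chance. A similarity check therefore cannot reveal confounding. All it does is decide, after data have been seen, which of several analyses is run.

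The default branch also leaves out the baseline value, which is commonly the best single predictor of a later score. Adjusting for it gains precision whether or not the arms happen to be balanced. Reserving it for visible imbalance gives up that gain in most trials.

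At stake are the precision and the pre-specification of two named secondary outcomes. The Discussion singles out QoL as an area where earlier studies reported benefit, so readers will look at this result.

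**Working it through.** **Inputs.** From the protocol article: 135 patients per group (Sample size calculation), two-sided 5% level (Statistical analysis), median survival of 8 months in control and 8 + 4 = 12 months in test (Sample size calculation). The article gives no effect size, standard deviation or power for QoL or markers, so it has no figure of its own to reproduce here. The correlation r between baseline and follow-up is not given either; it is assumed to be 0.3, 0.5 or 0.7.

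**1. Variance of the between-arm difference**, with equal variances at baseline and follow-up, relative to the follow-up-score t-test:
- t-test on follow-up scores: 1
- t-test on change from baseline: 2(1 − r)
- ANCOVA: 1 − r²

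ANCOVA has the smallest variance for any r strictly between 0 and 1.

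**2. Power where ANCOVA has 80%.** The standardised effect detectable by ANCOVA is (1.960 + 0.842) × √(1 − r²) × √(2/135), which is 0.325, 0.295 and 0.244 for the three correlations. The sample size then cancels:
- follow-up score: Φ(2.802 × √(1 − r²) − 1.960)
- change score: Φ(2.802 × √((1 + r)/2) − 1.960)

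| r | Follow-up-score t-test | Change-score t-test | 135 per arm is worth, under ANCOVA (follow-up / change) |
|---|---|---|---|
| 0.3 | 76% | 62% | 123 / 88 |
| 0.5 | 68% | 68% | 101 / 101 |
| 0.7 | 52% | 73% | 69 / 115 |

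The last column is 135 × (1 − r²) and 135 × (1 + r)/2. The change score does better than the follow-up score only when r exceeds 0.5. A repeated-measures ANOVA that includes baseline as a time level uses the baseline much as a change score does.

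**3. The whole rule.** Assume that *similar* means a baseline t-test with p above 0.05; the article does not say so. A correctly randomised trial then reaches ANCOVA only about 5% of the time. The rule was simulated with a follow-up-score t-test as default (60,000 null and 40,000 alternative runs per correlation):
- power 76%, 68% and 53% at r = 0.3, 0.5 and 0.7
- type I error 0.048, 0.042 and 0.037

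With a change-score default, type I error was 0.041, 0.043 and 0.046. The rule is slightly conservative.

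**4. Patients available for complete-row repeated-measures ANOVA.** Assume exponential survival at the planning medians. Day 126 is 126/30.4375 = 4.14 months.
- control deaths: 1 − 2^(−4.14/8) = 0.301, leaving about 94 of 135
- test deaths: 1 − 2^(−4.14/12) = 0.213, leaving about 106 of 135

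As an extreme lower bound, suppose nobody dies in the first 3 months and the medians stay the same. Deaths are then 1 − 2^(−1.14/5) = 0.15 and 1 − 2^(−1.14/9) = 0.08.

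**The case against.** **False positives.** A reader might infer that the rule inflates the false-positive rate. If the observed baseline imbalance is z = 1.9, just inside a 5% switch, and r = 0.5, the unadjusted test has a conditional error of P(|N(0.5 × 1.9, 1 − 0.25)| > 1.96) = 12%. That is one extreme point, under a switch the article does not state. The same formula gives 2.4% at z = 0 and 4.8% at z = 1, and the rule as a whole stays below 5% in the simulation. The documents do not support a claim of overall inflation.

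**Deaths.** A reader might also infer that the plan discards patients who die. The article does not say this. It names the methods but neither complete-row handling nor the visits analysed, and a t-test at one visit does not need complete rows across visits. Handling of death and missing data may sit in a full protocol or SAP that is not shown, so silence on it is no fault. The 30% and 21% are conditional on complete-row analysis and on exponential survival. The latter may overstate early deaths, since entry requires an expected survival of more than three months.

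**Other points that stand.** The size of the precision loss depends wholly on an assumed correlation. The trial is powered on overall survival only, and these outcomes are secondary. Listing within-arm comparisons is not itself a fault, because between-arm comparisons are listed too.

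None of this touches the central point. The rule is written in the article rather than left to another document, and it makes adjustment the exception.

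**Conclusion.** The concern holds as a matter of precision and pre-specification. The choice of method depends on an undefined baseline comparison that is uninformative after randomisation. Against an always-adjusted analysis with 80% power, the unadjusted default gives about 76%, 68% or 52% on follow-up scores, and about 62%, 68% or 73% on change scores, at correlations of 0.3, 0.5 and 0.7. The direction of the loss is certain for any correlation strictly between 0 and 1; its size rests on the assumed value.

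The rule does not raise the overall type I error and does not bear on the survival conclusion. Loss of up to about 30% of control and 21% of test patients to death by day 126 is a possible further cost if classical repeated-measures ANOVA is run on complete rows. It is not something the plan states it will do. The rule should be changed, but it does not threaten the trial's main result.

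**What to change.** Delete the similarity condition and adjust for the baseline value in every case. Preferably, name one mixed model for repeated measures for each outcome over the treatment-period visits (days 21 to 126), with baseline value, arm, visit, arm-by-visit interaction and centre, using all available visits. Report the between-arm difference with its interval as the result.

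This model keeps the earlier visits of patients who later die or miss assessments. It has no QoL value after death, so the analysis plan should say how the estimate is to be read in view of deaths, unless it already does.

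The cost is a change of wording and one model specification, made before the statisticians are unblinded. No new data, visits or patients are needed.
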